## Abstract

**Background::**

Enteral nutrition (EN) therapy is a routine supportive method for patients in the intensive care unit (ICU). However, the incidence of EN intolerance is prevalent, because most ICU patients suffer intestinal mucosal barrier damage and gastrointestinal motility disorder. There is no definite index to predict EN intolerance, and the current treatment methods are not effective in alleviating EN intolerance. Gut microbiota is an important component of the intestinal micro-ecological environment, and alterations in its structure and composition can reflect changes in intestinal function and microenvironment. The purpose of this study is to investigate the effect of EN on the gut microbiota of ICU patients by monitoring the dynamic alterations of gut microbiota and to screen out the microbial markers that can be used to predict the incidence of EN intolerance.

**Methods::**

One hundred ICU patients with trauma or in a period of acute stress after surgery will be enrolled, and their fecal samples will be collected at different timepoints for microbial sequencing and analysis. General clinical data (demographic information, surgical data, laboratory parameters, illness severity scores, and therapeutic drugs), nutritional status data (nutritional status assessment and nutrition therapy monitoring data), as well as clinical outcomes, will be recorded. The microbial and clinical data will be combined to analyze the baseline characteristics and dynamic alterations of gut microbiota along with the incidence of EN intolerance. Data related to the gut microbiota will be statistically analyzed by R software, and other data performed by SPSS23.0 software.

**Conclusions::**

The effect of EN on gut microbiota and microbial markers predicting the intolerance of EN will lead us to develop a new nutrition intervention strategy for ICU patients. Furthermore, the results of this study will provide a basis for the discovery of potential probiotics used for the prevention and treatment of EN intolerance.

## Introduction

1

Nutritional status is an important factor that directly affects the outcome of intensive care unit (ICU) patients and is closely related to the survival of ICU patients.^[1]^ At present, nutritional supportive approaches used in clinical practice include enteral nutrition (EN) and parenteral nutrition,^[2]^ and the former has advantages in maintaining the integrity of the intestinal barrier, preventing intestinal bacterial translocation, and reducing enterogenous infection. In addition, EN is more fit in with human physiology than parenteral nutrition and plays an irreplaceable role in the secretion and motility functions of the gastrointestinal tract.^[3–5]^

Early EN is widely accepted and used in the field of critical care medicine. However, for ICU patients, the implementation of EN is accompanied by great risks and challenges. The incidence rate of EN intolerance is very high. Severe trauma, shock, and postoperative critical patients are difficult to tolerate EN, and very few even occur nonobstructive intestinal necrosis. Retrospective analysis of nutrition practice data from 1888 patients in 167 ICUs worldwide found that the incidence rate of interruption of feeding due to EN intolerance was as high as 30.5% (576/1888), and clinical symptoms of EN intolerance appeared on average within 3 days (range: 1–12 days).^[6]^ For ICU patients, the need for nutrition is urgent, and if the application of EN is blocked due to intolerance, it will cause a second hit to the patients and hurt the prognosis of the patients. Therefore, it is an urgent task to reveal the causes of EN intolerance in ICU patients under stress state and to find effective treatment methods.

Although many researchers have tried to explore the causes of EN intolerance from the demographic or clinical characteristics, no appropriate laboratory or clinical indicators have been found to guide the nutritional supportive treatment.^[7–12]^ Gungabissoon U et al^[6]^ conducted demographic statistics on patients with EN tolerance and intolerance in ICU, and found that there were no statistical differences in age, gender, body mass index (BMI), and disease severity between the 2 groups. Lavrentieva A et al^[13]^ also found that there were no statistical differences in age, sex, burn index, burn area percentage, Acute Physiology, and Chronic Health Evaluation II score and sequential organ failure assessment score between septic burn patients with EN tolerance and intolerance.

Due to the unclear mechanism, there is still a lack of objective indicators for the evaluation and monitoring of EN intolerance. The accuracy and reliability of judging EN tolerance of critically ill patients based on clinical symptoms are limited. Gastrointestinal motility and gastric residual volume can be determined by ultrasound or gastrointestinal drainage volume, which is also a monitoring method. However, there is still no conclusion on how much residual amount can be determined as gastric emptiness, and its sensitivity is poor due to the wide range of determination of residual amount.^[14–16]^ Meanwhile, despite various drugs and treatment attempts, people are still often forced to discontinue enteral feeding due to severe EN intolerance.^[17–22]^

The gut microbiota plays an important role in maintaining the intestinal function, and the changes in the structure and composition of gut microbiota under stress state may be related to EN intolerance. The intestinal micro-ecosystem is known as the “second genome” and “second brain” of the human body. Gut microbiota and host depend on and restrict each other to maintain the normal physiological and health status. The composition of gut microbiota reflects the intestinal microenvironment and intestinal function of the host.^[23]^ In recent years, with the development of 16S ribosomal RNA (rRNA) and metagenomic sequencing technology, the role of gut microbiota in the occurrence of human diseases has been increasingly studied. In the field of intensive care medicine, a series of studies have been conducted on the relationship between gut microbiota and bacterial translocation, enteric infection, antibiotic resistance, antibiotic-associated diarrhea, acute respiratory distress syndrome, etc,^[24–30]^ yet there are few studies on gut microbiota and nutrient metabolism. Tremaroli et al^[31]^ studied the gut microbiota of patients after weight loss surgery and found that the composition of gut microbiota directly affects the amount of energy the host can obtain from the diet. On the other hand, the dietary structure also has a profound impact on gut microbiota. Both high-fat diet and obesity phenotype have been repeatedly proven to be associated with microbial migration.^[32]^

In the past, it was generally believed that the composition of EN should meet the metabolic needs of the host, without considering its effect on gut microbiota. It seems that this view has some limitations given that there exists an interaction between the host and the gut microbiota. As the composition of gut microbiota in ICU patients is closely related to the enteral nutrient uptake, the study on the relationship between gut microbiota and EN will shed light on the mechanism of EN intolerance and lay a foundation for the establishment of a new nutritional intervention strategy for ICU patients.

## Methods

2

### Study aim

2.1

The study aims to observe the effect of EN on the gut microbiota of ICU patients, and screen microbiological markers for predicting EN intolerance in ICU patients.

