### Study design and setting

2.2

The study protocol is designed to adhere to The SPIRIT (Standard Protocol Items: Recommendations for Interventional Trials) 2013 Statement.^[33]^ The present trial is a prospective cohort study conducted in a high-volume integrated ICU at the Beijing Tiantan Hospital, Capital Medical University, China. This study protocol was reviewed and approved by the Institutional Review Board of Beijing Tiantan Hospital, Capital Medical University (KY 2019-077-03). The study has been registered in the Chinese Clinical Trial Registry with the registration number ChiCTR2000031760. All eligible patients will be systematically proposed to participate in the study. After written informed consent has been obtained, patients will be enrolled. A flow diagram of this study is shown in Figure 1, and the schedule of the enrollment and assessments according to SPIRIT requirements is shown in Figure 2.

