### Study population

2.3

Patients will be included if they meet all the following criteria:

(1)Adult patients (≥18 years old)(2)Patients in acute stress stage after neurosurgery or intracranial trauma(3)Patients with tracheal intubation(4)Patients who expected to receive treatment for >=7 days in ICU.

Patients will be excluded from the study if they meet any of the following exclusion criteria:

(1)Patients transferred from other hospitals(2)Patients who had received EN before inclusion(3)Patients who have been in the ICU for more than 3 days(4)Patients who have contraindications to EN (e.g., mechanical, or paralytic intestinal obstruction, gastrointestinal bleeding; prone position patients)(5)Patients who have undergone gastrostomy or jejunostomy(6)Patients who have undergone rectal operation or with perianal infection.

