#### Nutritional status data

2.4.2

(1)Nutritional status assessment: nutritional risk screening 2002^[34]^ (the ESPEN endorsed screening tool based on BMI, weight loss and appetite as well as acute illness)^[2]^(2)Nutrition therapy monitoring data: initiate time of EN, feeding amount, response to feeding, albumin, pre-albumin, total lymphocyte count, glucose, electrolytes (potassium, magnesium, phosphate)

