#### Feces collection and preservation

2.5.1

Fecal samples will be collected on admission and days 3 and 7. For patients hospitalized in the ICU for longer than 14 days, an additional fecal sample will be collected on day 14. All fecal samples will be collected by inserting a sterile rectal swab into the anus 1 to 2 cm and rotating the swab 3 to 4 times. The swabs will be placed in a sterile Eppendorf tube and immediately stored in a refrigerator at −80°C until use.

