## Discussion

3

Nutritional status is closely related to the prognosis of critically ill patients, and nutrition support is an important part of the treatment for these patients. However, at present, the focuses of nutritional therapy on ICU patients are still restricted to the amount of energy to provide, the route to choose for energy supply, the feeding tube placement, and nitrogen balance, etc. What is ignored is that how these exogenous nutrients interact with the host and what effect will they take.

Gut microbiota is a complex ecosystem in the host, and changes in gut microbiota due to environmental impacts can affect the host's overall health. Particularly, critical illness is considered one of the major environmental factors that can affect the stability of the normal intestinal environment. Recent studies reported that when patients were in the ICU, the alpha-diversity of their gut microbiota declined and the gut microbiota was characterized by depletion of potential “health-promoting” commensal genus (e.g., *Faecalibacterium*, *Ruminococcus*, or *Pseudobutyrivibrio*) and overgrowth of pathobionts such as *Enterococcus*, *Escherichia*, *Staphylococcus*, Enterobacteriaceae, and *Pseudomonas*.^[29,35–37]^ Since more than 60% of ICU patients are forced to discontinue EN due to EN intolerance, and there is still no effective treatment method, it is urgent to seek new treatment methods to improve the situation. Exploring the composition and function of gut microbiota in ICU patients receiving EN may help to clarify the causes of EN intolerance and develop better strategies for EN treatment.

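### The first aim claims an effect of EN on the microbiota, but the text gives no contrast or analysis that separates EN from elapsed ICU time

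*Protocol article*

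**What the plan says.** - **Aim.** Section 2.1: "The study aims to observe the effect of EN on the gut microbiota of ICU patients". The abstract says that this effect will be investigated by following the microbiota over time. Its conclusions expect the effect of EN to lead to a new nutrition strategy.
- **Design.** Section 2.2: "The present trial is a prospective cohort study conducted in a high-volume integrated ICU". No unfed or delayed-EN group is described, and section 2.3 excludes patients with contraindications to EN.
- **Swabs.** Section 2.5.1: "Fecal samples will be collected on admission and days 3 and 7", and "For patients hospitalized in the ICU for longer than 14 days, an additional fecal sample will be collected on day 14". The text ties none of these to the start of EN.
- **Eligibility.** Section 2.3 excludes "Patients who had received EN before inclusion" and also "Patients who have been in the ICU for more than 3 days". A pre-feed swab is therefore possible, but up to 3 days of ICU time may precede inclusion.
- **Exposure data.** Section 2.4.2 collects "initiate time of EN, feeding amount" and the response to feeding. Section 2.4.1 collects antibiotics, proton pump inhibitors, probiotics and severity scores.
- **Analysis.** Section 2.9 names a Kruskal–Wallis test for species abundance. It names no grouping, EN term, ICU-day term or adjustment for that test.
- **Competing cause.** The Discussion cites studies showing that "when patients were in the ICU, the alpha-diversity of their gut microbiota declined", with overgrowth of pathobionts.

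**The concern.** An effect of EN is a causal claim. It needs a comparison between more EN and less EN at the same point in the ICU course. In this cohort, days on EN and days in the ICU rise together, and antibiotics and acute stress run alongside. The Discussion already expects diversity to fall in the ICU, so a fall from admission to day 7 would be unsurprising without any feeding effect.

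At stake is the first of the two aims, and the part of the abstract's conclusion that would build a nutrition strategy on it. The second aim, markers that predict intolerance, does not need this causal attribution and is not affected.

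**Working it through.** **1. What the plan's own figure covers.** Section 2.8 gives 89 evaluable patients, about 100 after 10% attrition. The figure reproduces as a one-sample test of 40% against a fixed 57% (two-sided 5%, 90% power):

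n = [(1.960·√(0.57·0.43) + 1.282·√(0.40·0.60)) / 0.17]² = 88.4, rounded up to 89; 89/0.9 = 98.9.

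This sizes the intolerance rate. It says nothing about precision for the microbiota aim.

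**2. What the named test can show.** Section 2.9 does not name the groups for the Kruskal–Wallis test.
- If they are swab days, the test compares ICU days, with EN and ICU time mixed.
- If they are tolerance groups, it serves the second aim and not the first.

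Neither reading contrasts EN exposure at a fixed ICU day.

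**3. How much separation the recorded data allow.** The documents give no distribution of EN start times, so the following inputs are assumptions: 90 patients, swabs on ICU days 0, 3 and 7, mean start at day 1.5, SD of start from 0 to 2 days, and no start before day 0.

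For a patient first fed on day s, with s between 0 and 3, days on EN at the three swabs are 0, 3−s and 7−s. At s = 1.5 they are 0, 1.5 and 5.5.
- Within-patient sum of squares at s = 1.5: 0² + 1.5² + 5.5² − 7²/3 = 16.17.
- A patient who starts δ days from the mean departs from the common pattern by (0, −δ, −δ). Centred within patient, this is (⅔δ, −⅓δ, −⅓δ), with sum of squares ⅔δ².
- Share of EN-day variation not explained by ICU day ≈ ⅔·SD² / (16.17 + ⅔·SD²).

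At SD 0.5 this gives 0.167/16.33 = 1.0%. At larger SDs the approximation is too high because starts are cut off at day 0, so the table gives simulated values. The variance inflation factor (VIF) is 1/share, and the standard error grows by its square root, relative to a model with patient effects but no ICU-day term.

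| SD of EN start (days) | Share left after ICU day | VIF | SE multiplier |
|---|---|---|---|
| 0 | 0% | infinite | – |
| 0.25 | 0.25% | 397 | 19.9 |
| 0.5 | 1.0% | 102 | 10.1 |
| 1 | 3.4% | 30 | 5.5 |
| 1.5 | 6.1% | 16 | 4.1 |
| 2 | 9.1% | 11 | 3.3 |

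**4. Where that contrast comes from.** It compares patients who started EN earlier with those who started later, at the same ICU day. Start time was not assigned, so illness severity can drive both it and the microbiota. Feeding amount adds a further contrast, but the Introduction notes that feeding is interrupted for intolerance, so amount may partly reflect gut function.

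**The case against.** The strongest reply has four parts.

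- **The aim is only to observe, under usual care, and the Discussion gives prediction and monitoring as the overarching objective.** This is fair as to emphasis. The aim and the abstract's conclusion still speak of an effect of EN.
- **The analysis may be specified elsewhere.** The article is condensed, the SAP is not shown, the two figures are not visible, and the abstract says microbial and clinical data will be combined. The absence of a detailed model is therefore not an error in itself. What stands is that the stated design has no unfed contrast and the stated test is unadjusted. A later analysis plan can use the recorded exposure but cannot add a comparator.
- **The data are not hopeless.** This is correct. A reader might infer that the EN effect is not identifiable at all. That would hold only if every patient started EN at the same time and feeding amount gave no contrast. Start time and amount are recorded per patient, so weak separation is the supported statement.
- **The baseline is protected.** Excluding prior EN makes a pre-feed swab possible, though section 2.5.1 does not require the first swab to precede the first feed.

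Two further inferences are tempting and are not supported. One is that a patient enrolled on ICU day 3 has no interval between the first and day-3 swabs. That takes the first swab from enrolment and day 3 from ICU admission, and the text does not mix the clocks in this way. The other is that swabs should be re-timed from EN start. With swabs on EN days 0, 3 and 7, ICU day equals a patient constant plus EN day. The two would then move one-for-one within every patient, and the within-patient contrast in step 3 would disappear.

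**Conclusion.** The point holds in this form: the text offers no contrast or stated analysis that separates EN from elapsed ICU time, acute stress and antibiotics, so following it as written would not support attributing microbiota change to EN. With the recorded data, EN is at best weakly separable, through differences between patients in start time and feeding amount.

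The size rests on assumed start times. For SDs of 0.25 to 2 days, 0.25% to 9.1% of the variation in EN days remains after ICU day, with standard errors about 20 to 3.3 times larger. The actual start-time distribution would replace these figures. They cover days on EN only, exclude any contrast from feeding amount, and do not allow for confounding by severity.

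**What to change.** 1. Keep the ICU-day swab schedule. Require the first swab to be taken before the first feed (the swab is fitted around feeding as it happens, with no change to care), and record ICU day at every swab, since up to 3 ICU days may precede inclusion.
2. For the first aim, replace the unadjusted rank test with a repeated-measures model of the microbiota measures. Enter EN exposure at each swab (days since EN start and feeding amount, both already collected) as time-varying terms, adjusted for ICU day, antibiotics and illness severity. Treat day 14 with care, because only patients staying longer than 14 days contribute.
3. Report the EN estimate with its confidence interval. Unless the model separates EN from ICU time, restate the aim and conclusion as changes in the gut microbiota during EN.

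The cost is a short amendment and modest extra analysis, with no added swabs. The EN estimates will probably be imprecise, and the stated conclusion will be less ambitious.

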### Study design and setting

2.2

The study protocol is designed to adhere to The SPIRIT (Standard Protocol Items: Recommendations for Interventional Trials) 2013 Statement.^[33]^ The present trial is a prospective cohort study conducted in a high-volume integrated ICU at the Beijing Tiantan Hospital, Capital Medical University, China. This study protocol was reviewed and approved by the Institutional Review Board of Beijing Tiantan Hospital, Capital Medical University (KY 2019-077-03). The study has been registered in the Chinese Clinical Trial Registry with the registration number ChiCTR2000031760. All eligible patients will be systematically proposed to participate in the study. After written informed consent has been obtained, patients will be enrolled. A flow diagram of this study is shown in Figure 1, and the schedule of the enrollment and assessments according to SPIRIT requirements is shown in Figure 2.

**Figure 1 F1:**
[figure not shown]
Flow diagram of this study. ^∗^NRS2002: is a nutritional risk screening tool that the ESPEN endorsed based on BMI, weight loss, and appetite as well as acute illness. BMI =  body mass index, EN = enteral nutrition, NRS 2002 = nutritional risk screening 2002, OTU = operational taxonomic units.

**Figure 2 F2:**
[figure not shown]
Schedule of enrolment and assessments according to SPIRIT.

### Study population

2.3

Patients will be included if they meet all the following criteria:

(1)Adult patients (≥18 years old)(2)Patients in acute stress stage after neurosurgery or intracranial trauma(3)Patients with tracheal intubation(4)Patients who expected to receive treatment for >=7 days in ICU.

Patients will be excluded from the study if they meet any of the following exclusion criteria:

(1)Patients transferred from other hospitals(2)Patients who had received EN before inclusion(3)Patients who have been in the ICU for more than 3 days(4)Patients who have contraindications to EN (e.g., mechanical, or paralytic intestinal obstruction, gastrointestinal bleeding; prone position patients)(5)Patients who have undergone gastrostomy or jejunostomy(6)Patients who have undergone rectal operation or with perianal infection.

### Clinical data collection

2.4

We will obtain all clinical notes including general and nutritional specific data recorded in each patient's health record during their stay in the ICU.

#### General clinical data

2.4.1

(1)Demographic information: ID, sex, age, weight (kg), height (cm), BMI calculation (kg/m^2^), comorbidities, smoking history, drinking history, medication history(2)Surgical data: clinical diagnosis, surgical site, operative time, the amount of intraoperative blood loss and blood transfusion, intraoperative hypotension (mean arterial pressure <65 mm Hg) duration(3)Laboratory parameters: blood count, platelet count, lymphocyte ratio, creatinine, liver tests (aspartate aminotransferase, alanine aminotransferase, gamma-glutamyl transferase, alkaline phosphatase), bilirubin(4)Illness severity scores: Glasgow, Acute Physiology, and Chronic Health Evaluation II, and sequential organ failure assessment(5)Therapeutic drugs: proton pump inhibitors, prokinetics, gastric mucosal protectors, coagulants, anticoagulants, antibiotics, vasopressors, anti-diarrhea medicine, cathartics, probiotics(6)Clinical outcomes: duration of mechanical ventilation, length of ICU stay, length of hospital stay, mortality, infections

